#### Physical measurements

Participants’ height will be measured at baseline to the nearest 0.1 cm using a stadiometer. Weight will be measured both at baseline and follow-up using a digital scale (SC-240 MA, Tanita Japan). Weight will be recorded to the nearest 0.1 kg.

#### Process evaluation measures

##### Adherence measures

For the control group, adherence to daily weighing will be measured by calculating the proportion of days for which we have a recorded weight measurement on the BodyTrace server.

For the intervention group, adherence to daily weighing will be assessed by calculating the proportion of days for which a weight was recorded in the weight tracking app or in the daily action planning questionnaire. Adherence to weight-tracking will be calculated as the proportion of days for which a weight measurement was recorded in the app. Adherence to action planning and reflection will be measured by calculating the proportion of days on which the respective questionnaires were completed. An overall adherence score will be calculated averaging adherence rates across all intervention components.

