## Methods

### Study design and setting

An individually randomised, two arm, parallel group design will be employed, assessing superiority of the self-regulation intervention over daily self-weighing alone. Participation will last 8 weeks. This length was deemed sufficient to assess early effectiveness of the intervention, as previous studies have been able to detect weight loss effects after 2 months.^28^ If the results are promising, the data will provide good evidence to justify conducting a longer-term randomised controlled trial. Participants will attend two study visits, one at baseline and one after the end of the eighth week of the intervention. The primary outcome will be weight change. The study will take place in Oxfordshire, UK, and run between April and October 2019.

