Reflecting: The think-aloud study showed that participants struggled to interpret day-to-day weight changes due to daily fluctuations that were not caused by fat loss or gain.^12^ We therefore decided to encourage reflection on a weekly rather than daily basis. Participants will receive weekly emails with feedback on their weekly weight trends, asking them to complete an online questionnaire (Qualtrics, USA). The questionnaire will prompt reflection on the relationship between behaviours performed throughout the week and weight change observed. Participants will be asked to use this insight to evaluate the use of the weight loss actions they had performed throughout the week.Action Planning: We aimed to strike a balance between ensuring that participants choose appropriate actions and allowing them to choose actions themselves, as lack of goal ownership predicts attrition.^23^ Participants will therefore choose one weight loss action per day from a list of 53 actions (see online supplementary appendix 1). To create the actions list, we first identified weight loss actions from effective weight loss interventions in the literature. These were reviewed, adapted and complemented during iterative brainstorming sessions with an interdisciplinary expert team, comprised of dietitians, GPs and psychologists. The rationale for daily action plans was twofold: (1) allowing participants to adapt their actions flexibly to their day and (2) giving participants exposure to a wider range of strategies. Based on action planning and implementation intention research, which shows that the specificity of action plans increases likelihood of implementation,^33–35^ we will ask participants to specify where, when and how they will perform their chosen action, which cues they will use, which barriers they might experience and how they will deal with them.As participants only reflect on their behaviour on a weekly basis, we grouped the actions conceptually into seven categories, five of which cover diet-related actions and two of which cover physical activity-related actions. Participants will be asked to choose one category at the beginning of the week, and choose daily actions from this category for the rest of the week. Weekly behaviour reflection will therefore focus on the effectiveness of a category of actions. Taken together, the reflection and action planning process shall enable participants to experiment with different weight loss approaches and decide on their effectiveness and usefulness based on trends in weight data. At the beginning of weeks two through eight of the intervention, participants will be prompted to commit to some of the actions of previous weeks, as the performance of several weight loss actions increases chances for weight loss. Action planning support will be provided through daily questionnaires (Qualtrics, USA), which will be sent to participants every morning via email.

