What	*Self-weighing*: Participants will be instructed to weigh themselves daily using simple digital body scales (Etekcity Corporation, California). They will be asked to weigh themselves in a similar state every day, ideally first thing in the morning and without clothes. *Weight tracking:* Participants will be asked to download the free app “Weight Loss Tracker, BMI” by aktiWir GmbH on their smartphone and use it on a daily basis to record their weight measurements. They will be asked to submit a backup of their data to the research team every week. *Action* *p* *lanning:* Participants will receive a daily questionnaire helping them to plan a weight loss action. The questionnaire will start by asking participants to enter their morning weight. At the beginning of first week, they will then be asked to choose a category of actions, and they will be able to choose one of the actions within this category per day for the rest of the week. There are seven categories in total, five covering diet-related actions and two covering physical activity-related actions. Participants will be asked to specify for each action how, when and where they are going to perform it, and which cues they are going to use. They will also be prompted to think about how to overcome potential barriers. At the start of weeks 2 through 8, participants will be encouraged to try out a new category of actions. We will additionally ask participants on a weekly basis to commit to continuing some of the actions they tried out in previous weeks. In order to help participants to maintain an overview of the actions they performed so far, we will provide them with a non-digital action plan diary. *Report email:* Once a week, participants will receive an email from the research team, informing them about their trend weight change for the last week. This trend weight change consists of the slope of a trend line fitted across all measurements of the week, multiplied by the number of days covered by the measurements. The weight measurements used to create these reports will be taken from the daily action planning questionnaires. *Reflection and* *a* *ction* *e* *valuation:* In the weekly report email, participants will receive a link to the reflection and action evaluation questionnaire. This questionnaire prompts participants to think about why their weight has changed as it has. They are further asked to evaluate the group of actions they performed across the week, including whether they found them useful and whether they would repeat them. On the basis of this evaluation, participants will be able to decide which actions they want to continue doing in the next weeks, and which ones to drop. Using this method of self-experimentation, participants will be able to try and test different weight-loss strategies and identify the ones that are effective and sustainable for them.	Self-weigh every morning in a similar state, using smart scales (BodyTrace, New York).

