### Measurements

A schedule of measurements can be found in table 2.

**Table 2 T2:** Schedule of measurements

	Screening	Baseline visit	Intervention period	Completion email	Follow-up visit (after 8 weeks)
Length	10 min	Up to 1 hour	10 min per day	5 min	up to 45 min
Who conducts	Research team	Research team	Participants	Research team	Research team
Eligibility assessment	☑	☑ (BMI)			
Enrolment		☑			
Baseline questionnaire		☑			
Weight		☑	☑		☑
Height		☑			
Allocation		☑			
Weight tracking (only intervention)			☑		
Daily questionnaire (only intervention)			☑		
Weekly report and questionnaire (only intervention)			☑		
Final questionnaire (only intervention)				☑	
Semistructured interview (20 participants in intervention group)					☑

BMI, body mass index.

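### Adherence to the weekly reflection questionnaire is scored per day, so a fully adherent participant gets 14% and the overall adherence score cannot exceed 79%

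*Protocol article*

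**What the plan says.** The definition stands in the protocol article under Process evaluation measures, Adherence measures. For the intervention arm it sets four rates: daily weighing, weight tracking, action planning and reflection. The first two are proportions of days. The last two share one sentence: "Adherence to action planning and reflection will be measured by calculating the proportion of days on which the respective questionnaires were completed". The section then combines the rates: "An overall adherence score will be calculated averaging adherence rates across all intervention components". It states no weights.

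The two questionnaires run on different schedules:

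- **Action planning** (Intervention section): "Action planning support will be provided through daily questionnaires (Qualtrics, USA), which will be sent to participants every morning via email".
- **Reflection** (same section): "We therefore decided to encourage reflection on a weekly rather than daily basis". Table 1 (TIDieR checklist, row What) agrees: "In the weekly report email, participants will receive a link to the reflection and action evaluation questionnaire". Table 2 also lists this questionnaire as weekly.

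Adherence to the self-regulation steps is the first secondary outcome listed, and adherence measures are among the planned moderators of effectiveness. The Statistical analyses section repeats that adherence will be examined as a moderator of weight change.

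**The concern.** A per-day denominator suits a task that falls due every day. Applied to a task that falls due once a week, it makes six days in seven count as missed even when the participant has done everything asked.

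Three things are at stake:

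- **The reported rate.** Reflection is one of the three self-regulation steps that the intervention prompts. Shown beside the other rates, it would look like the component participants neglected most, purely because of how it is scored.
- **The overall score.** Its ceiling falls below 100%, and reflection has almost no influence on it, although a plain average implies that each component counts equally.
- **Uses of the score.** A moderator analysis based on the overall score would inherit the distortion. So would the sampling of interviewees across levels of adherence (Follow-up section), if the overall score were used for it.

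**Working it through.** **Inputs**

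- Duration (Study design and setting): "Participation will last 8 weeks", so 8 × 7 = 56 days.
- Action planning questionnaires: one a day, 56 in all.
- Reflection questionnaires: one a week. The article does not state the number sent. I take eight, and show seven in case none follows the last week.
- Overall score: unweighted mean of the four rates defined for the intervention arm.

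The article gives no maximum or expected adherence figure, so there is nothing to reproduce first.

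**Maximum reflection rate as written** = questionnaires completed / days

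- Eight sent: 8/56 = 14.3%
- Seven sent: 7/56 = 12.5%

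**Maximum overall score as written** = mean of the component maxima

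- Four rates, eight sent: (1 + 1 + 1 + 0.143)/4 = 78.6%
- Four rates, seven sent: (1 + 1 + 1 + 0.125)/4 = 78.1%
- Weighing and tracking merged into one component, eight sent: (1 + 1 + 0.143)/3 = 71.4%

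**With a weekly denominator**, the reflection maximum is 8/8 = 100% and the overall maximum is (1 + 1 + 1 + 1)/4 = 100%.

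**Influence of reflection on the overall score** (four rates, eight sent)

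| | As written | Weekly denominator |
|---|---|---|
| All reflections against none | 0.143/4 = 3.6 points | 1/4 = 25 points |
| Missing half of them | (0.143 − 0.071)/4 = 1.8 points | 0.5/4 = 12.5 points |

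**Ranking of two participants**

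| | As written | Weekly denominator |
|---|---|---|
| A: 100% on the three daily tasks, no reflections | (3 + 0)/4 = 75.0% | (3 + 0)/4 = 75.0% |
| B: 90% on the three daily tasks, all reflections | (2.7 + 0.143)/4 = 71.1% | (2.7 + 1)/4 = 92.5% |

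As written, A ranks above B. With the weekly denominator B ranks well above A. The rule therefore changes the order of participants as well as the scale.

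**The case against.** The best defence is that the sentence is loosely worded and the authors meant days on which a questionnaire was due. They plainly know that reflection is weekly: Table 1 and the list of secondary outcomes both say so when they discuss adherence. The analysis plan, in a supplementary appendix not at hand, may set the denominator properly. That is possible, but the article does not say it. Every other rate in the section is a plain proportion of days, and an analyst who follows the sentence gets 14%. The point is a rule that conflicts with the article's own schedule; it does not rest on missing detail.

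A second argument limits the harm, and much of it stands:

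- If the reflection rate is used alone as a moderator, dividing by 56 instead of 8 rescales it by a constant 1/7. The coefficient changes, but the test statistic, p-value and ranking do not.
- The only adherence rate defined for the control arm is daily weighing, which is correctly a proportion of days. The between-arm comparison of that rate is untouched.
- The article names adherence measures as moderators without saying that the overall score is the one used. Since that score is defined under the heading Adherence measures, it is fair to read it as included, but this is a reading.
- The primary outcome, sample size and primary analysis are unaffected, and the rate can be recalculated from stored completions at any time.

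**Conclusion.** The point holds: the definition is wrong as written. Full adherence to reflection scores 14.3%, and the overall score has a ceiling of 78.6%.

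The 14.3% assumes eight weekly questionnaires; with seven it is 12.5%. The ceiling also assumes that the four rates are averaged separately with equal weight, which is the plain reading. Seven questionnaires, or merging weighing with tracking, lowers it further.

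The damage is confined to the reported reflection rate, the overall adherence score and whatever uses that score. Within those limits it matters, because a listed secondary outcome would be misreported and the composite can put participants in the wrong order. It should be corrected before the adherence data are analysed.

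**What to change.** Replace the shared rule with two. Action planning adherence is the number of daily questionnaires completed divided by the 56 intervention days. Reflection adherence is the number of weekly questionnaires completed divided by the number of weekly questionnaires sent, with that number stated (eight, if one follows each week). Weighing and tracking keep their daily denominators. Compute the overall score from these rates, and name the four components and their equal weights so that the score is reproducible. If the analysis plan already uses a weekly denominator, bring the protocol wording into line with it.

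The cost is a sentence or two of definition. Completion of both questionnaires is already recorded, so no new data collection is needed, and nothing in the primary analysis changes.

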##### Evaluation of intervention components

Using the data from the final online questionnaire, we will calculate means and SDs of the ratings for each intervention component.

### Retention

The daily questionnaire and weekly report emails will act as prompts for the participants to engage with the intervention. At the end of the follow-up visit, participants will receive a £35 one4all gift card.

There are no criteria for withdrawal other than participants’ request to withdraw. Participants can also ask to withdraw their collected data. We will ask participants wishing to withdraw whether they are willing to attend the final follow-up and take part in an exit interview to understand the reasons for their discontinuation.

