#### Exclusion criteria

The participant may not enter the study if any of the following apply:

Unable to understand English.Unable to follow all intervention procedures for a period of more than four consecutive days.Currently self-monitoring body weight more than once a week.Currently or within 3 months of study entry attended a weight management programme or currently participating in another weight loss study.Lost more than 5% of current body weight in the last 6 months.Prior bariatric surgery or scheduled for bariatric surgery.Pregnant or planning to become pregnant during the course of the study.Have an electronic medical implant, such as a pacemaker.Have ever had or been diagnosed with an eating disorder.People that the GP judges not able to meet the demands of either treatment programme or measurement schedule. This may include severe medical problems not listed above.

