#### Baseline

When the participants attend the baseline appointment, a member of the research team will seek informed consent and check eligibility for inclusion in the study by measuring height and weight for BMI calculation. The participants will be asked to complete an online questionnaire, capturing demographics (ie, age, gender, ethnicity) and previous experiences with self-weighing. Participants will be randomised and receive instructions for the assigned intervention. The researcher will provide participants with a body scale for the duration of the trial. A follow-up appointment will be scheduled for after the completion of the intervention period.

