
10.1136/bmjopen-2019-031572.supp1Supplementary data

At baseline, participants will receive detailed instructions about the intervention with the aid of a manual which they may take home afterwards. The manual will explain the rationale of self-regulation and experimentation to participants and give tips on how to best weigh on a daily basis. It will also provide information on the different weight loss actions participants can try throughout the study. Participants will also be given an action diary, in which they will be asked to record their performed weight loss actions.

We will call participants at the end of the first and fourth week to ask about and solve any technical problems that may have arisen (eg, with the functioning of the scales or the receiving of questionnaires). A figure from the study manual depicting the intervention procedure is displayed in figure 2. The Template for Intervention Description and Replication (TIDieR) checklist^36^ for the PREVAIL intervention and the comparator is reported in table 1.

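### The participant's own request is the only stated criterion for stopping, so no written trigger pauses weighing or weight-loss prompts if pregnancy, an eating disorder or serious illness arises during the 8 weeks

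*Protocol article*

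**What the plan says.** The Retention section of the protocol article gives one route out: "There are no criteria for withdrawal other than participants’ request to withdraw". It adds that people who wish to withdraw will be asked whether they would still attend the final follow-up and give an exit interview, "to understand the reasons for their discontinuation".

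The exclusion criteria list two conditions that bear on this point: "Pregnant or planning to become pregnant during the course of the study" and "Have ever had or been diagnosed with an eating disorder". They also exclude "People that the GP judges not able to meet the demands of either treatment programme or measurement schedule", and note that this can cover severe medical problems not otherwise listed.

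During the 8 weeks the intervention arm receives daily action-planning questionnaires, "which will be sent to participants every morning via email". These go out automatically (Table 1, How). The arm is also telephoned "at the end of the first and fourth week to ask about and solve any technical problems". The control arm is told to weigh daily and gets no further instructions (Control).

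The Adverse events section says that none will be collected, because a difference between arms is considered implausible. The Trial monitoring section says that there are no stopping rules and no steering or data monitoring committee. The Trial management group section makes that group responsible for seeing that participants are safeguarded.

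**The concern.** The plan treats pregnancy and eating disorder as reasons not to start, and severe illness as a possible reason. All three can begin after randomisation. The plan then closes the list of reasons for stopping at the participant's own wish, and it describes no contact that asks about health. A person who would not have been enrolled could go on being prompted each morning to weigh and to plan a weight-loss action, unless they volunteer the change and someone decides case by case what to do.

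What is at stake is the welfare of a small number of people and clarity for staff about when to act. It is not the trial's statistical conclusion.

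**Working it through.** No arithmetic sizes this point, because the documents give no rate of pregnancy, eating disorder or serious illness during follow-up. The check is a reading of the relevant sections side by side.

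1. **Is the rule closed or merely silent?** It is closed. The Retention sentence does not leave other criteria unmentioned; it says that there are none.

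2. **Does withdrawal there mean leaving the study or stopping the programme?** It includes stopping the programme. People who withdraw may still attend the final follow-up and are asked why they discontinued. Someone who is still weighed at 8 weeks has not left data collection; what they have stopped is the programme.

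3. **Which conditions matter?** The exclusion criteria name pregnancy and eating disorder outright. Severe illness enters through the GP's judgement, and the reason given is feasibility: being unable to meet the demands of the programme or the measurement schedule. No reason is given for the first two. That they bear on safety is an interpretation; pregnancy could also be excluded because it changes body weight, the primary outcome.

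4. **Does any described contact ask about these conditions?** None does.
   - The calls in weeks 1 and 4 concern technical problems and go to the intervention arm only.
   - The weekly questionnaire asks why weight changed and how useful the actions were (Table 1, What).
   - The control arm has no scheduled contact between the two visits.

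5. **Does another section supply a trigger?** It does not. Adverse events are not collected and there are no stopping rules. The Trial Management Group's safeguarding duty is general and names no event, question or action.

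6. **What happens if the text is followed as written?** The questionnaires in the intervention arm are sent automatically, so they continue until someone intervenes. In the control arm the instruction to weigh daily simply stands.

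**The case against.** The strongest reply is that this is a condensed article. Pause procedures and requests to report a change often sit in the information sheet, the manual or the full protocol, none of which is shown. That stands in part: the information sheet may already ask participants to report such changes, and nothing here should be read as saying that it does not. It does not remove the point, because a further criterion for stopping the programme, wherever it was written, would contradict the Retention sentence.

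A second reply is that the team can already act. That also stands. The Trial Management Group must safeguard participants, and the chief investigator both organises the mailings and is the primary contact for everyone (Table 1, Who), so a disclosure would reach someone able to stop the emails. A reader might infer from the Retention sentence that the team is barred from pausing anyone. The documents do not support that. What is missing is a stated trigger, not the power to act.

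A third reply is that light monitoring was a reasoned choice in a short trial with self-chosen actions and ethics approval, and that the entry criteria already remove people planning pregnancy or with any history of eating disorder. This limits how many people could be affected. But the reason given for not collecting adverse events is that the arms are unlikely to differ. That does not answer what to do when an excluded condition arises for any cause.

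**Conclusion.** The point holds as a minor participant-safety improvement, to consider rather than to require. The closed withdrawal rule leaves no written trigger for pausing the programme when a condition relevant to entry arises during it.

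It rests on two readings: that withdrawal in the Retention section includes stopping the programme, which the follow-up invitation and exit interview support; and that the pregnancy and eating-disorder exclusions have a safety element, which the protocol does not state. Few participants are likely to be affected, but no figure can be given.

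Two stronger conclusions are not supported. A reader might infer that participants are being exposed to harm; no section shows harm from daily weighing or from choosing one action a day. A reader might also infer that the primary analysis is compromised; participants are analysed by allocated arm whether or not they stop, so the sample size and the validity of the estimate are unaffected.

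**What to change.** Replace the Retention sentence with text to this effect:

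> Participants may withdraw on request. If the team learns of pregnancy, an eating disorder or serious illness in a participant in either arm, the weighing instruction and any prompts are paused while the Trial Management Group decides on continuation with clinical input. Anyone paused or stopped is still invited to the 8-week weighing and is analysed as randomised.

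At the baseline visit ("Participants will be randomised and receive instructions for the assigned intervention"), ask everyone in both arms to tell the team if such a change occurs. This is not weight-loss guidance, so it leaves the control condition intact. Because the request is the same in both arms, it does not make detection differ by design. Health questions added only to the intervention arm's calls or emails would do so for little gain, and are not recommended. No adverse event form or new committee is needed.

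The cost is one replaced sentence and one spoken sentence at about 100 baseline visits, submitted as an amendment if judged substantial. The statistical downside is slight dilution of the intention-to-treat effect if an intervention participant is paused. As an illustration, the Sample size section implies 100 × (1 − 0.20) / 2 = 40 followed up per arm. One participant who loses a full 1.5 kg effect would lower the mean difference by 1.5 / 40 = 0.0375 kg. That figure describes the price of the change, not the size of the problem. A paused person might also be less likely to attend the 8-week weighing, which is why the invitation should be written into the rule.
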